##### Characteristics of the individuals

The CFIR dimension of ‘characteristics of the individuals’ encompasses knowledge and beliefs about the intervention, self-efficacy and other personal attributes of the staff participants at SVLFG [43]. The degree of normalisation among staff-participants (e.g. field workers, in-house staff, call centre agents) is assessed by the German translation of the NoMAD and 3 additional normalization questions; the questionnaire (20 items) refers to the normalisation process theory and assesses the extent to which the new implemented service is a normal part of the daily routine at work [104]. The NoMAD questionnaire is characterized by a high internal consistency (α = 0.89) and has already been validated in heterogeneous samples [105, 106]. Determinants of behavioural change (e.g. knowledge, belief, self-efficacy) are assessed with the Discriminant Content Validation of the TDF Questionnaire (DCV) with 32 items [107] among field workers, in-house staff and call centre agents. The DCV helps to understand factors that influence the behaviour in health care settings and can therefore makes it possible to improve the implementation of innovations. Additionally, about 20 focus groups using an interview guide based on TDF [45] with field workers are conducted to identify barriers and facilitating factors for advising on prevention services. The aim of this mixed-method approach is the optimisation of the implementation process or interventions based on the findings.

##### Implementation process

To capture the implementation process, the number and type of implementation and dissemination activities of SVLFG, GET.ON and IVP are reported every 3 months with an excel file (e.g. date, place, organisation, setting of the activity, target group, number of participants and content / aim of the activity). Implementation costs are reported every 3 months with an excel file and are defined according to the EU-project ImpleMentAll^2^ project as the sum of personnel costs and other direct and indirect costs (indirect costs calculated at 20% of direct costs). In addition, the implementation team is interviewed every 6 months, particularly with regards to perceived effectiveness of the implementation in general and based on individual implementation strategies. These interviews also discuss barriers and facilitating factors in the implementation process and assessment of the current state of implementation. Quantitative (referral and uptake rates, barriers and facilitating factors in the implementation) and qualitative results (focus groups) about the progress and quality of implementation are prepared and delivered to the implementation team every 6 months to promote adaptions and improvements.

#### Maintenance

In assessing the maintenance of the implemented internet- and tele-based interventions, follow-up surveys with the insured participants will be conducted 12 months after first contact for the prevention project (e.g. 12 months after first login at the GET.ON platform or registration at IVPnet) to monitor the long-term impact of preventive interventions on mental health (see effectiveness measures, 60–65). Referrals to the SVLFG call centre are reported by the external service providers to capture all processes in the implementation that contribute to sustainable development. Uptake rates of the internet- and tele-based interventions are monitored in the maintenance phase of the respective rollout region. In terms of sustainability, we also record the use of a second IMI, the maintenance phase of the IMIs (e.g. monthly contacts for a year) or the prolongation of an IVP tele-based coaching and any other health care utilisation.

Normalisation is recorded in the maintenance phase using the questionnaire NoMAD [104] at the staff-level (e.g. field workers, in-house staff, call centre agents), and will be compared to the normalisation degree during the implementation phase. Additionally, the attitudes and experiences of the staff-participants involved in the implementation process are essential for sustained implementation. Therefore, a concluding survey with the staff-participants and important multipliers at SVLFG (e.g. management board) will be conducted at the end of the project to assess their professional view on the implementation and their intention to further use the internet- and tele-based prevention services. To ensure practical relevance, the item pool for this survey will go through an iterative feedback process with the initiators of the project.

#### Measuring implementation success

In line with the ImpleMentAll,^3^ implementation success is defined as an increase in uptake of internet- and tele-based interventions (referral rates and levels of uptake, e.g. not started, in treatment, completer, non-completer), degree of normalisation among staff-participants (extent to which consultation to the internet- and tele-based interventions are perceived as a normal part of work) and efficiency outcomes (costs of implementation effort in relation to uptake and degree of normalisation).

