## Methods

### Design of the study

This study is a prospective, longitudinal implementation study and is described according to the Standards for Reporting Implementation Studies (StaRI) checklist [49], see Supplementary material. A mixed-methods approach using qualitative interviews, focus groups, quantitative surveys and reporting data is utilised for a comprehensive understanding of the implementation process. The evaluation is based on the RE-AIM framework [42] and the CFIR [43].

The implementation follows a stepwise, nationwide rollout plan which determines the availability of the internet- and tele-based interventions and the enrolment of the insured persons in each rollout region. Each region (2–7 federal states of Germany) undergoes these implementation phases at different times, starting with a pilot implementation phase in Bavaria and Schleswig-Holstein for 1.5 years and following with three rollouts (A, B and C) over 2 years. The initial pilot implementation phase was extended for various reasons (e.g. additional time needed to implement internal structures at SVLFG such as the referral process and documentation of consultations with insurers, additional time to conduct trainings, and unforeseen delayed availability of the tele-based coaching). Based on the Conceptual Model of Implementation Phases [50], the study can be divided into the following phases: exploration, preparation, implementation (6–12 months) and maintenance (12–24 months). The duration of the phases was defined in accordance to the RE-AIM framework that recommends 6 to 12 months for the implementation phase and at least 2 years for the maintenance phase [42]. In addition, the enrolment plan of the SVLFG stipulates that the rollout area is expanded every 6 months and focuses on implementation in this region within these 6 months Fig. 1.

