#### Reach

To assess reach, the number and characteristics of the potentially eligible insured individuals at SVLFG, as well as exclusion, referral and uptake rates of the internet-, tele-based and on-site group preventive services will be reported. The following uptake levels will be considered in order to illustrate different levels of engagement:
Referral rates: The absolute number of: a) referrals by the SVLFG field workers (operationalised as consultations about internet- and tele-based interventions), b) referrals by the call centre agents to the internet- and tele-based prevention services (IMIs: sending out a code for the registration at the online-platform, tele-based coaching: registration on the IVPnet platform), and c) the first contact with the external service provider (IMIs: first log in at online-platform to symptom screening; tele-based coaching: agreement for first tele-based coaching appointment).Uptake rates of internet- and tele-based interventions:

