Intervention not started: The absolute number of referred persons who completed the assessment phase (IMIs: psycho-diagnostic assessment, tele-based coaching: first coaching assessment session) after the first contact with the external service provider, but have not started the intervention.In treatment: The absolute number of persons who have started the intervention after assessment phase (IMIs: first login into first module; tele-based coaching: receive tele-based coaching at minimum second session).Treatment not completed: Absolute number of persons who completed less than 50% vs. 70% of the intervention (IMIs: completed less than 50% vs. 70% maximal online modules within 13 weeks, have not logged in for at least 8 weeks or have interrupted the training for other reasons; tele-based coaching: completed less than 50% vs. 70% of the total call minutes, did not answer for at least 8 weeks or cancelled the coaching for other reasons).Treatment completed: a) In previous e-mental health studies, the completer criteria differed between 50 to 100% of completed units [81–84]. Research also indicates that a minimal treatment for subthreshold depression (e.g. six phone calls each with a maximum of 15 min) can also be effective in preventing MD [85]. Therefore, we defined two criteria with different treatment dosis as following: Absolute number of persons who completed at least 50% vs. 70% of online modules or call minutes. b) Clinical judgment by coaches at GET.ON Institute and IVPNetworks assessed with the Helping Alliance Questionnaire (HAQ) based on 11 items [86] in order to supplement the quantitative criteria for completion.Uptake of other services: This may include the crisis hotline, a second guided IMI, diagnostic clarification at IVPNetworks (via telephone or on-site), referrals to social or health service centres (e.g. socioeconomic or family consultants) during the tele-based coaching.

In addition, the estimated number of people exposed to recruitment materials and the associated response rate will be assessed. Specific recruiting strategies are tested to examine successful ways of addressing the target population. To provide representative information, interested but not participating individuals, and enrolled participants will be compared based on routine data. Differences in reach between the internet-, tele-based and on-site preventive services will be investigated as well.

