#### Quantitative analysis

The evaluation of the implementation follows the RE-AIM dimensions as described above. Descriptive analyses (frequencies, means and percentages) will be performed to assess outcomes across all RE-AIM dimensions. We will evaluate the implementation success of the internet- and tele-based interventions separately.

To assess the representativeness of the participants compared to the target group, t-tests or non-parametric tests will be used. To assess intervention effectiveness, we analyse for different groups of participants (e.g. participants who have started treatment or completed treatment) by using independent sample t-test and chi-squared analyses. We will use t-tests or non-parametric tests to analyse differences between pre-, post- and follow-up-measurements. In order to counteract the issue of multiple comparisons, Bonferroni correction is used. The statistical significance level is set to *p* < .05. Within-group effect sizes and 95% CIs will be reported at all measurement points. Implementation effectiveness is assessed by comparing uptake rates, the degree of normalisation among staff-participants and efficiency outcomes (costs of implementation effort in relation to uptake and degree of normalisation) at different time points.^4^

Furthermore, linear regression models are used to investigate differences between the interventions (guided IMIs, personalised tele-based coaching and on-site group workshops) regarding reach outcomes (referral and uptake rates) with intervention type as independent variable. By using further linear regression models we compare socio-demographic and clinical outcomes as dependent variables between the participants of the different prevention services (independent variable). Based on multiple linear regression models we analyse the influence of factors at staff level (credibility of the internet- and tele-based interventions, degree of normalisation, leadership support, organisational readiness to change and determinants of behavioural change) as independent variables on the number of referrals by field workers, in-house staff and call centre agents (dependent variables). Additionally, the implementation outcomes will be compared between the federal states and rollout areas at different phases of implementation.

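### The uptake component of implementation success is an increase in absolute counts while the population offered the services grows by design, so expansion alone can meet it

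*Protocol article*

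**What the plan says.** All references are to the Protocol article.

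- **Measuring implementation success:** "implementation success is defined as an increase in uptake of internet- and tele-based interventions (referral rates and levels of uptake". The levels listed there include not started and non-completer as well as in treatment and completer. The other two components are staff normalisation and "efficiency outcomes (costs of implementation effort in relation to uptake and degree of normalisation"). No denominator, reference period or minimum increase is given.
- **Reach:** "Referral rates: The absolute number of: a) referrals by the SVLFG field workers". The same form is used downstream: "In treatment: The absolute number of persons who have started the intervention after assessment phase", and for completion "Absolute number of persons who completed at least 50% vs. 70% of online modules or call minutes". The not-started and not-completed levels are also counts.
- **Design of the study:** areas open in steps under this arrangement: "stepwise, nationwide rollout plan which determines the availability of the internet- and tele-based interventions and the enrolment of the insured persons in each rollout region". On the pace of opening it adds that "the rollout area is expanded every 6 months and focuses on implementation in this region within these 6 months". A region comprises 2 to 7 federal states, and a 1.5-year pilot in two states came before rollout A.
- **Group 1: insured persons at SVLFG:** 465,000 members are eligible nationwide, 500 to 800 participants are expected, and enrolment is said to depend on the rollout stage.
- **Quantitative analysis:** uptake rates, normalisation and "efficiency outcomes (costs of implementation effort in relation to uptake and degree of normalisation) at different time points" are compared. Implementation outcomes are also compared between federal states and rollout areas by phase.

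**The concern.** The quantities are called rates but defined as counts. A count depends on how many people are offered the service and on how readily each of them takes it up. The rollout plan raises the first every 6 months, and only the second says whether implementation is working. The success definition does not separate them.

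Two related problems follow. A comparison of areas by raw count partly ranks them by size. And because not started and non-completer stand among the levels whose increase is success, more people dropping out along the way would also count in favour.

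Uptake is the first-listed success criterion and serves the first two research questions. Referral and uptake rates go back to the implementation team every 6 months, and the Discussion links long-term feasibility to success. A service losing ground per member could be reported, and fed back, as gaining on uptake.

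**Working it through.** The article gives no threshold or expected increase for uptake, so there is no figure of the plan's own to reproduce. The calculation below is an illustration.

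**Inputs from the article:** 465,000 eligible members; 500 to 800 expected participants (used only for scale); expansion every 6 months; data collection April 2019 to April 2021, that is, four half-years.

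**Assumptions (not in the article):** A opens in half-year 1, B in 2, C in 3. The pilot states are either open throughout or left out. Three sets of member shares were tried. Uptake per eligible member is constant.

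**Formulas:** rate r = total participants ÷ sum over half-years of eligible members in open areas. Count in half-year t = r × eligible members open in t. Break-even fall in r = 1 − (first open population ÷ last open population).

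| Shares pilot/A/B/C (%) | Areas counted | Eligible members open, half-years 1 to 4 | Counts for a total of 500 | Last ÷ first | Break-even fall |
|---|---|---|---|---|---|
| 25/25/25/25 | with pilot | 232,500; 348,750; 465,000; 465,000 | 77; 115; 154; 154 | 2.00 | 50% |
| 40/20/20/20 | with pilot | 279,000; 372,000; 465,000; 465,000 | 88; 118; 147; 147 | 1.67 | 40% |
| 10/30/30/30 | with pilot | 186,000; 325,500; 465,000; 465,000 | 65; 113; 161; 161 | 2.50 | 60% |
| 25/25/25/25 | A to C only | 116,250; 232,500; 348,750; 348,750 | 56; 111; 167; 167 | 3.00 | 67% |

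First row: r = 500 ÷ 1,511,250 = 0.331 per 1,000 per half-year; 0.331 × 232.5 = 77 and 0.331 × 465 = 154. A total of 800 scales the counts by 1.6 and leaves the ratios unchanged. The ratio for A to C is 3.00 whenever the three rollouts are equal in size.

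**Falling uptake:** in the last row, a 25% fall in per-member uptake still gives 3 × 0.75 = 2.25, and a halving gives 3 × 0.5 = 1.5. If counts were reported cumulatively (first row: 77, 192, 346, 500) they could not fall at all. The article does not say whether counts are cumulative or per period.

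**Within one area:** services are not offered there before rollout, so a count taken at R0 is about zero and any later count exceeds it. From R1 on, counts per period within an area can fall.

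**Same data per member:** with r constant, uptake per 1,000 eligible members in open areas is 0.331 in every half-year of the first row, so last ÷ first = 1.00 and no increase appears.

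**Which model can estimate the change:** suppose only months 1 to 12 of each area are used, with region and calendar-time effects. A covers half-years 1 and 2, B covers 2 and 3, C covers 3 and 4. Take calendar effects 0, 1, 2, 3 and region effects 0, −1, −2. Their sum is 0 in each area's first half-year and 1 in its second, which is exactly the late-versus-early indicator. The contrast is therefore not identified; splitting half-years into quarters changes nothing. Using A's later months breaks the dependence: with all months after the first six counted as late, A requires equal calendar effects in half-years 2 and 3, while B requires them to differ by 1.

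**The case against.** A reader might infer that the rollout by itself guarantees a finding of success. The article does not support that. Success has three components. Normalisation is a staff questionnaire score at R0 to R3 that can fall and that adding regions does not raise, and cost relative to uptake can worsen.

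A reader might also take all counts to start at zero. That holds only inside a newly opened area; nationally, the pilot states were already running. R0 to R3 are the staff-survey times, uptake is reported every 3 months, and nothing makes R0 the reference for it.

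Finally, the efficiency wording might be read as rewarding a higher cost per user. The natural reading of more efficiency is the opposite, and the text fixes no direction. The defect is at most an unstated direction.

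There is also mitigating text. Percentages are promised across all RE-AIM dimensions, and a recruitment response rate is planned. The Adoption section describes the number of insured people by region and state. Uptake is monitored by region in the maintenance phase, and sustainability is read at R3, timed from each area's rollout. So falling per-member uptake need not go unseen. The study is largely descriptive, and a footnote to the time-point comparison is not in the text at hand.

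These points limit the reach of the finding. They do not remove it, because none of them is tied to the success definition as a denominator or reference period.

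**Conclusion.** The point holds for the uptake component. As defined, it can show an increase through expansion alone, and it compares areas on counts from populations of different size. At constant per-member uptake, the half-yearly count rises about 1.7- to 2.5-fold with the pilot states and 3-fold for three equal rollouts without them. Per-member uptake could fall by 40 to 60%, or by 67%, before the last count stopped exceeding the first. These sizes rest on assumed shares and opening dates; the direction needs only that the open population grows, which the article states. The efficiency ratio is affected because it uses the same counts. Normalisation is not driven up by expansion, so the overall success conclusion is not predetermined.

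**What to change.** - **Rates:** define referral and uptake as events per 1,000 eligible insured members in open areas per quarter, within region and aligned to time since that region's rollout. State that counts are per period.
- **Downstream levels:** express assessed, started and completed as proportions of the previous step, so that more not-started or non-completer cases do not count as success.
- **Reference:** name a post-rollout reference period, for example the first 6 months after R0, rather than R0 itself.
- **Model, if one is used:** Poisson or negative binomial regression with log eligible member-months as offset and region effects. Add calendar-time terms only if later months or pilot-region data are included.
- **Efficiency:** state that success means a lower implementation cost per started or completed participant.

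Cost: mainly wording and a small modelling change. Referral and uptake reports already arrive every 3 months, and the Adoption section plans regional membership figures. Table 1 lists eligible-member numbers at 18 months only, so counts by region must be secured. The uptake criterion becomes harder to meet.

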### Analysis

Reporting of implementation results will follow the StaRI [49] statement. To assess the implementation success and to illustrate a broad picture of the implementation process in the context of rural areas we will combine qualitative and quantitative methods in a summative way. Quantitative and qualitative data are collected simultaneously to evaluate the implementation process. Qualitative data are used to provide a deep understanding, while quantitative data are used to provide breadth of understanding [108]. In addition, the results of the qualitative analysis are then validated in a quantitative survey. Qualitative surveys are only carried out on a small part of the sample, while all participants are invited to the respective quantitative surveys. The database is therefore larger for quantitative surveys. The analysis is based on guidelines for mixed-methods research defined by the NIH Office of Behavioural and Social Sciences Research [109]. In addition, the Consolidated criteria for reporting qualitative studies (COREQ) [110] are used.

#### Quantitative analysis

The evaluation of the implementation follows the RE-AIM dimensions as described above. Descriptive analyses (frequencies, means and percentages) will be performed to assess outcomes across all RE-AIM dimensions. We will evaluate the implementation success of the internet- and tele-based interventions separately.

To assess the representativeness of the participants compared to the target group, t-tests or non-parametric tests will be used. To assess intervention effectiveness, we analyse for different groups of participants (e.g. participants who have started treatment or completed treatment) by using independent sample t-test and chi-squared analyses. We will use t-tests or non-parametric tests to analyse differences between pre-, post- and follow-up-measurements. In order to counteract the issue of multiple comparisons, Bonferroni correction is used. The statistical significance level is set to *p* < .05. Within-group effect sizes and 95% CIs will be reported at all measurement points. Implementation effectiveness is assessed by comparing uptake rates, the degree of normalisation among staff-participants and efficiency outcomes (costs of implementation effort in relation to uptake and degree of normalisation) at different time points.^4^

Furthermore, linear regression models are used to investigate differences between the interventions (guided IMIs, personalised tele-based coaching and on-site group workshops) regarding reach outcomes (referral and uptake rates) with intervention type as independent variable. By using further linear regression models we compare socio-demographic and clinical outcomes as dependent variables between the participants of the different prevention services (independent variable). Based on multiple linear regression models we analyse the influence of factors at staff level (credibility of the internet- and tele-based interventions, degree of normalisation, leadership support, organisational readiness to change and determinants of behavioural change) as independent variables on the number of referrals by field workers, in-house staff and call centre agents (dependent variables). Additionally, the implementation outcomes will be compared between the federal states and rollout areas at different phases of implementation.

According the intention-to-treat principle all observed data will be included. Patterns of missing data will be analysed and corrected. All analyses will be performed with R statistic software [111].

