#### Group 1: insured persons at SVLFG

Inclusion criteria for insured persons at SVLFG includes: being an insured member of the health insurance scheme OR the pension fund of the SVLFG, being an agricultural contractor OR a collaborating spouse OR a family member or a pensioner, being over 18 years old, having access to the internet and/or a telephone, and providing informed consent.

Persons will be excluded if they currently suffer from a mental disorder and need extensive therapeutic service. Individuals may be excluded during the consultation in the call centre (if the interested insured person reports a mental disorder), during the assessment by the service provider or during their participation in case of a suspected mental disorder. If there is a suspicion, the external service provider advises the participant that a consultation with a general practitioner is recommended. The insured individual gets support in the search for further treatment options. In addition, people can be excluded for the tele-based intervention, if they have substantial hearing impairment or for the online interventions, if they have a visual impairment.

There are 465,000 eligible insured members of SVLFG nationwide, and the sample size is not capped. The number of participants enrolled in this study depends on the rollout stage of the implementation. Eligible insured persons can choose the specific intervention based on their preference and needs which reflects the conditions of routine care. A sample size of *N* = 100 per intervention is desirable to achieve reliable results. Based on previous experiences in the pilot phase of the implementation in two federal states, we expect a sample size of approximately 500 to 800 participants for the national implementation area.

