### Measurements

The used measures are summarised in Table 1, followed by a description of each RE-AIM dimension and selected outcomes. Measurements include routine data, staff reviews of intervention consultations as well as usage of the interventions by insured individuals, online-assessments, qualitative interviews and focus groups.

**Table 1 Tab1:** RE-AIM dimensions, measures and assessments

Dimension	Measure	Source	Assessment type	Time point
**REACH (individual level)**	Number and characteristics of potentially eligible insured individuals	SVLFG	Routine data	18 m
	Exclusion, referral und uptake rates; Completer rating from clinician’s judgement (Helping Alliance Questionnaire)	GET.ON Institute / IVPNetworks / SVLFG; GET.ON and IVP coaches	Reportings; Online-Assessment	Every 3 months; after participant is defined as (non-) completer
	Estimated number of people exposed to the recruitment, recruitment response rate in general as well as specific recruiting strategies	GET.ON Institute / IVPNetworks / SVLFG	Reportings	Every 3 months
	Representativeness of participants compared to eligible insured individuals and interested, but not participating insured persons	SVLFG	Routine data	18 m
**EFFECTIVENESS (individual level)**	Depressive symptoms (Patient Health Questionnaire 9), perceived stress (Perceived Stress Scale 4), generalised anxiety disorder (Generalised Anxiety Disorder 7 scale), somatisation (Somatic Symptom Scale 8), health-related quality of life (Assessment of Quality of Life 4D), subjective capacity to work (Subjective Prognostic Employment Scale)	Insured person	Online-assessment	T0-T2^a^
	Patient satisfaction (Client Satisfaction Questionnaire adapted for internet interventions), side effects (Assessment of Negative Effects of Psychotherapy)	Insured person	Online-assessment	T1^a^
**ADOPTION (organisational level)**	Number, proportion and characteristics of involved employees per organisation, characteristics of federal states and rollout areas, characteristics of insured persons and type of agricultural holding	GET.ON Institute / IVPNetworks / SVLFG	Sociodemographics of employees, routine data	R0^b^ Continuous
**IMPLEMEN-TATION (individual + organisational level)**	*Characteristics of the interventions:*			
	- Adaptations (TIDieR checklist)	GET.ON Institute / IVPNetworks	Reportings	Mid and end of the project

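### Representativeness is assessed by significance tests, which mix the size of the difference with the number of participants; standardised differences with confidence intervals should carry the statement

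*Protocol article*

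**What the plan says.** Table 1 of the protocol article lists this as a Reach measure, taken from routine data at 18 months: "Representativeness of participants compared to eligible insured individuals and interested, but not participating insured persons". The Reach text repeats the comparison of enrolled participants with people who were interested but did not take part.

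The method is in the Quantitative analysis section: "To assess the representativeness of the participants compared to the target group, t-tests or non-parametric tests will be used". The same paragraph adds "In order to counteract the issue of multiple comparisons, Bonferroni correction is used" and "The statistical significance level is set to *p* < .05". It does not say whether the Bonferroni correction covers the representativeness tests, or how many comparisons it counts.

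Two further statements in that section bear on the point. Descriptive reporting is general: "Descriptive analyses (frequencies, means and percentages) will be performed to assess outcomes across all RE-AIM dimensions". Effect sizes and intervals are promised for another purpose: "Within-group effect sizes and 95% CIs will be reported at all measurement points". That covers change within participants over time, not the contrast between participants and the target group.

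On size, the section on insured persons states "There are 465,000 eligible insured members of SVLFG nationwide", calls 100 participants per intervention desirable, and expects about 500 to 800 in total.

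**The concern.** Representativeness asks how far participants differ from the people they are meant to stand for. A t-test or rank test asks whether the difference is exactly zero. With a reference group of 465,000, the precision of the comparison is set almost entirely by the number of participants, so the same skew can look unremarkable in a small sample and clearly significant in a larger one. Reading non-significance as representativeness rewards low enrolment. Reading significance as a lack of representativeness penalises high enrolment.

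The Bonferroni correction, if it applies here, pushes one way: the more characteristics are tested, the easier it is to find no significant difference on any of them. What is at stake is how one Reach outcome is interpreted. The effectiveness and cost results are not affected.

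**Working it through.** The article gives no power or precision figure for this comparison, so there is nothing to reproduce. The check asks what the stated test would return at the article's own sample sizes.

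**Inputs from the article:** N = 465,000 eligible members; n = 500 and 800 (expected total); n = 100 (desired per intervention, used here only to show the effect of n); significance level 0.05.

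**Assumptions:** two-sided tests (sidedness is not stated); normal approximation; SD = 1 in both groups; participants compared with the remaining N − n members; skews of 0.1 to 0.3 SD chosen for illustration; ten comparisons for the Bonferroni case.

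**Formulas:**
- SE = √(1/n + 1/(N − n))
- Smallest observed difference reaching p < .05, which is also the 95% CI half-width: 1.96 × SE
- p for an observed difference d: 2 × [1 − Φ(d/SE)]
- Chance of significance at a true difference d: Φ(d/SE − 1.96) + Φ(−d/SE − 1.96)

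**Results for d = 0.1 SD:**

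| n | SE | Smallest significant difference (SD) | p if 0.1 SD is observed | Chance of significance if 0.1 SD is true | 95% CI around an observed 0.1 |
|---|---|---|---|---|---|
| 100 | 0.1000 | 0.196 | 0.32 | 17% | −0.10 to 0.30 |
| 500 | 0.0447 | 0.088 | 0.025 | 61% | 0.01 to 0.19 |
| 800 | 0.0354 | 0.069 | 0.005 | 81% | 0.03 to 0.17 |

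Worked line for n = 800: d/SE = 0.1/0.0354 = 2.83, so p = 0.005, and the chance of significance is Φ(2.83 − 1.96) = Φ(0.87) = 81%.

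A binary characteristic behaves in the same way. With 55% among participants against 50% among members (assumed), the chance of significance is 17%, 61% and 81% at n = 100, 500 and 800.

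**Dependence on the size of the difference.** At n = 100, true skews of 0.1, 0.2 and 0.3 SD are significant 17%, 52% and 85% of the time. The test does respond to the size of the difference, but the result cannot be separated from n.

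**Bonferroni.** With ten comparisons the level is 0.05/10 = 0.005 and the critical value is 2.81. The smallest significant difference rises to 0.281, 0.126 and 0.099 SD at n = 100, 500 and 800. The chance of detecting a true 0.2 SD skew falls from 52% to 21% at n = 100, and from 99% to 95% at n = 500. Within the expected range of enrolment, an observed 0.1 SD then misses significance at n = 500 (0.1 < 0.126) and just reaches it at n = 800 (0.1 > 0.099).

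**Limit of the check.** The number of interested non-participants is not stated, so none of these figures applies to that second comparison. A smaller comparator would make it less precise.

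**The case against.** The strongest reply is that the article already plans frequencies, means and percentages across all RE-AIM dimensions, so raw differences will stand beside the tests, and that no rule says significance alone settles representativeness. Both points are correct and keep the matter small. They do not remove it: a table of means carries no precision and no common scale across characteristics, and the method named for assessing representativeness is the test.

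A second reply is that an article condenses a fuller plan, and that tabulation details and any relevance margin belong there. This is fair for those details. The choice of tests, however, is stated in the article itself, and the same paragraph specifies effect sizes and intervals only for within-group change.

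Three stronger readings are tempting and are not supported:
- A reader might infer that the test result reflects sample size and ignores the size of the difference. It reflects both, as the rise from 17% to 85% at n = 100 shows.
- A reader might infer that popular services will be judged unrepresentative and small ones representative. The article states no representativeness test per service. It compares participants overall and assigns socio-demographic comparisons between services to linear regression. The separate evaluation of internet- and tele-based interventions concerns implementation success, which the article defines by uptake, normalisation and efficiency.
- A reader might take a null result at n = 100 to rule out differences beyond 0.20 SD. That holds only if the observed difference is zero. A non-significant observed 0.19 SD has an interval reaching about 0.39 (0.19 + 0.196).

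**Conclusion.** The point holds in a limited form. The stated method fits the Reach question badly because its result confounds the size of the difference with enrolment. Against the full membership, a minor skew of 0.1 SD would be significant 61% to 81% of the time at the expected 500 to 800 participants, while at n = 100 an observed 0.1 SD gives p = 0.32. If the Bonferroni correction covers these tests, adding characteristics makes non-significance easier to reach.

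The figures rest on two-sided tests, equal SDs, a normal approximation and illustrative skews. The ten-comparison case is an assumption. The size of the problem is modest: it affects how one descriptive Reach outcome is worded, and planned descriptive tables soften it.

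**What to change.** For the overall comparison of participants with eligible members, and separately with interested non-participants, report a standardised mean difference or a difference in proportions with its 95% CI for each routine-data characteristic. Base the representativeness statement on these and keep p-values secondary. The estimate then no longer shifts systematically with n; only its precision does. An observed 0.2 SD would read 0.20 (0.00 to 0.40) at n = 100 and 0.20 (0.13 to 0.27) at n = 800.

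If a relevance margin is used, fix it in advance and allow an inconclusive reading when the interval crosses it. With 0.2 SD as an example only, the overall comparison could support a statement: the interval lies inside the margin for observed differences up to 0.2 − 0.088 = 0.11 at n = 500 and 0.2 − 0.069 = 0.13 at n = 800.

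Any breakdown by service or region should be descriptive only. At n = 100 the half-width is already about 0.20. If 500 to 800 participants were split equally over eight services and three rollouts (an assumption), cells would hold about 21 to 33 people, with half-widths of 1.96/√21 = 0.43 to 1.96/√33 = 0.34. No interval could then fall within a margin of 0.2.

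The cost is a change of analysis wording and slightly more reporting. The routine data are the same and recruitment is unaffected. The downside is that some statements will be less clear-cut than a significant or non-significant label.
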